## Design & methods

### The hypotheses

As detailed below, the primary hypothesis is that PPD is superior in effectiveness to a comunity treatment as usual control group (TAU) using the Hamilton Depression Rating Scale as its primary outcome measure. The study tests the effectiveness of psychoanalytic therapy with a research sample of patients suffering from TRD, as an exacting test of its hypothesised ability, both to reduce symptoms over the immediate term, and to yield significant reductions in long-term susceptibility to depression. The trial has been designed to test the effectiveness of the PPD model as it might be offered in the context of an ordinary psychotherapy clinic, to patients with long term mental health problems including major depression. The aim therefore was to stay as close as possible to the setting in which those patients with chronic TRD may be referred, and to offer the therapy in a form as little modified as possible, while meeting what is required by trial methodology. A pilot study of two cases was conducted before commencing the study proper, to obtain information about the practicalities of both the therapeutic and the research enterprises.

We employ an intention-to-treat methodology with all eligible, consenting participants. The participants are randomised into two groups: one receives a target of 60 sessions of once-weekly psychoanalytic psychotherapy for depression (PPD) over a period of eighteen months [in practice the actual number is allowed to vary slightly according to factors such as the timing of holidays], while the other represents a ‘treatment as usual’ (TAU) control condition. The PPD group is assessed over the trial intervention and for a two year follow-up. The TAU control group is observed over the same 3.5 year period.

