### The outcome measures

#### *Primary outcome*

In psychotherapy and antidepressant medication outcome research, the Hamilton Rating Scale of Depression (HRSD, [44]) is the most widely used interview-based measure of depressive severity [62]. Independent, double-rated HRSD scores have been chosen as the trial’s primary index of depression severity. The HRSD is a structured interview which quantifies the severity of depressive symptoms in patients already diagnosed as suffering from depressive disorder. The psychometric properties of the instrument are acceptable [63]. In addition to categorical depressed/not depressed analyses (with a score of 14 as the cut-off point of remission), we intend to model the trajectory of scores across the 3.5-year observation period. This will permit the assessment of the severity of depression over time, with a particular focus on the 2-year follow-up period.

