### The analysis of data

To preserve neutrality, no data will be analysed until all subjects have reached the six month follow-up point. An intention-to-treat analysis will be performed in the first instance (i.e. analysing all available data from randomised participants) using for all analyses the STATA, version 11.0 package. The numbers and percentages of losses to follow-up at 12, 18, and 24 months after randomisation will be reported and will be compared between the treatment arms with absolute risk differences (95% CIs). Any deaths and their causes will be separately reported. To increase the power and precision of the estimated treatment effect, missing baseline covariates will be imputed for our main analysis using either mean or regression imputation [77]. All available results will be used without missing outcomes being imputed. Primary analyses will be based on the assumption of ignorable drop-outs. In secondary analyses, missing values will be replaced by multiple imputations using Markoff Chain Monte Carlo methods [78].

For continuous outcome variables, the differences in mean score between those randomised to either arm of the trial will be examined using analysis of covariance adjusting by 1) baseline value of outcome 2) baseline value of the outcome, gender and age. The assumption of linearity will be assessed by residual analysis; if necessary, bootstrapping techniques will be employed. Sensitivity analyses will be conducted to take into account missing data using multiple imputation, which assumes data are 'missing at random'. For continuous response variables, statistical analyses will be based on linear mixed models [79].

For binary responses, mixed-model logistic regression models and generalized estimating equations will be used [80]. Logistic regression will be used to compare proportions of patients that have lost their diagnosis during the treatment and follow-up period in the two groups using an HRSD of 14 as criterion. Analysis of 'time to first recovery' and ‘time to first relapse’ outcome will also be conducted using survival analysis methods and the log-rank test for bivariate comparisons and Cox's proportional hazards to adjust for gender, stratification variables and time spent on treatment prior to randomisation. The dependencies between design points in the case of linear mixed models will be accounted for by assuming an unstructured correlation structure.

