Statistical significance will be tested with the Wald test, and CIs will be established by the Delta method [81]. Time will be handled as a categorical variable with five possible values - 0, 6, 12, 18, 24 months. The basic model will include the main effects of time, of treatment group, of the difference between theoretical and realised date of measurement and first order interaction of time and treatment. A complete model will include potential confounding factors (e.g. age group, gender etc). Complementary analyses will be carried out adjusting for the baseline level of outcome measures. 'As treated' models will be carried out by including variables describing compliance (e.g. waiting time from randomisation to initiation, degree of participation, including an indicator whether the patient received the study treatment) and auxiliary treatments such as medication.

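### The linear mixed model ends at 24 months and so gives no HRSD treatment effect for the last 18 of the 24 follow-up months, although the protocol promises a 3.5-year trajectory

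*Protocol article*

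**What the plan says.** The Primary outcome section of the protocol article names the HRSD and says, beyond the categorical analyses, that "we intend to model the trajectory of scores across the 3.5-year observation period", "with a particular focus on the 2-year follow-up period". The section on the hypotheses gives the same time frame for the control arm: "The TAU control group is observed over the same 3.5 year period". Table 2 lists HRSD at baseline, at 3, 6, 9, 12, 15 and 18 months, and at three follow-up visits labelled 6, 12 and 24 months.

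The section on the analysis of data then specifies the linear mixed model. On time it says: "Time will be handled as a categorical variable with five possible values - 0, 6, 12, 18, 24 months". The fixed effects are time, treatment group, the deviation of the actual from the planned measurement date, and the "first order interaction of time and treatment". Dependence between design points "will be accounted for by assuming an unstructured correlation structure".

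On attrition, the same section says: "The numbers and percentages of losses to follow-up at 12, 18, and 24 months after randomisation will be reported". The arms are to be compared at those times by absolute risk differences.

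**The concern.** Two explicit statements conflict. One promises HRSD over 42 months with emphasis on the two years after treatment. The other fixes a model that ends at month 24, six months after treatment. The visits at months 30 and 42 are collected but have no place in that model.

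The hypotheses section sets two aims for the therapy: a reduction of symptoms in the near term and a lower long-term susceptibility to depression. Late follow-up bears on the second. If the model is run as written, the continuous HRSD analysis is silent on that aim beyond six months after treatment.

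If the model is instead extended informally, the late time points may be chosen after results are known, because the protocol allows analysis to begin once every participant has reached the six-month follow-up.

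The attrition comparison has the same gap. The limitations section expects high attrition in a trial of this length, yet no comparison by arm is planned at the two latest visits.

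**Working it through.** **1. Put the visits on one clock.** Treatment lasts 18 months (section on the test intervention). Month from randomisation = 18 + follow-up month.

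- 6-month follow-up: 18 + 6 = 24
- 12-month follow-up: 18 + 12 = 30
- 24-month follow-up: 18 + 24 = 42

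The last visit is at 42 / 12 = 3.5 years, which reproduces the protocol's own observation period. The section on the Tavistock psychodynamic interview confirms the clock: it places the repeat interview two years after entry, six months after therapy ends.

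**2. Compare the follow-up visits with the model.** The levels are 0, 6, 12, 18 and 24.

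| HRSD follow-up visit | Month | In the model |
|---|---|---|
| 6 months | 24 | yes |
| 12 months | 30 | no |
| 24 months | 42 | no |

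- Follow-up covered: (24 − 18) / (42 − 18) = 6 / 24 = 25%
- Follow-up not covered: 42 − 24 = 18 months
- Observation period covered: 24 / 42 = 57%

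**3. Check which contrasts can be estimated.** With categorical time, the treatment difference at month t is the treatment main effect plus the interaction term for level t. Terms exist only for listed levels, and a categorical factor does not extrapolate. The contrasts at 18 and 24 months are therefore estimable, and those at 30 and 42 months are not. A rank check of the design matrix gives the same answer, and shows all four estimable once the later visits are levels. The date-deviation covariate adjusts for the timing of visits already in the model and does not bring in others.

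**4. Test whether the levels could be months of follow-up.** They could not. Table 2 has no 18-month follow-up visit, and the attrition sentence in the same section counts 12, 18 and 24 months from randomisation.

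**5. Cost of extending the factor.** An unstructured covariance matrix for k time points has k(k + 1)/2 parameters, variances included.

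| Levels | k | Parameters |
|---|---|---|
| 0, 6, 12, 18, 24 (as stated) | 5 | 5 × 6 / 2 = 15 |
| 0, 6, 12, 18, 24, 30, 42 | 7 | 7 × 8 / 2 = 28 |
| all ten scheduled HRSD visits | 10 | 10 × 11 / 2 = 55 |

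The limitations section gives a sample of 129.

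**The case against.** The best defence is staging. Analysis may begin once all participants have reached the six-month follow-up, which is month 24, and both the time factor and the attrition points end exactly there. The data analysis section could then describe a first analysis, with the 3.5-year trajectory to follow. This may well explain where the 24 came from. But the article nowhere calls the model interim, and it specifies no later one. Its intention-to-treat analysis comes first, but that may only set it apart from the as-treated analysis.

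A second defence is that other analyses reach later. This stands in part. The logistic analysis of lost diagnosis refers to treatment and follow-up, the time-to-recovery and time-to-relapse analyses carry no stated 24-month cut-off, and the analysis of covariance names no time point. None of these models the course of HRSD scores. The growth curves mentioned in the Discussion could do so, but that passage is a general remark with no model specified.

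A third is that the section promises to use all available results, so the short list may be incomplete wording. If so, the list still contradicts the promise and needs correcting.

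Two stronger readings are tempting. A reader might infer that the trial cannot assess any effect during follow-up. The documents do not support this: the model includes month 24, and the analyses just named may extend further. A reader might also count the 3-, 9- and 15-month visits and call the omission of 5 of 9 post-baseline visits the defect. That does not follow either. The protocol promises a trajectory, not the use of every quarterly score, and a six-monthly grid during treatment is defensible with an unstructured covariance and 129 participants.

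**Conclusion.** The time factor is wrong as written. Set against the primary outcome section and Table 2, it leaves out two of the three HRSD follow-up visits (months 30 and 42). The linear mixed model therefore cannot estimate the treatment effect over the last 18 of the 24 follow-up months, the period on which the protocol says it will focus. The comparison of losses by arm falls short by the same 18 months.

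The conclusion is limited to the stated mixed model and the stated attrition comparison. It assumes that the model's months count from randomisation, which the attrition sentence and the visit schedule both support, and that no unpublished plan already supersedes the list. It does not depend on effect size, power or sample size.

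**What to change.** - Extend the time factor to at least 0, 6, 12, 18, 24, 30 and 42 months.
- Report the treatment-by-time contrast at 18 months (end of treatment) and at 42 months (end of follow-up).
- Compare losses by arm at 30 and 42 months as well as at 12, 18 and 24.
- If a first analysis at 24 months is intended, say so, and specify the later model alongside it.

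The cost is a change of wording, slightly more analysis work, and 28 − 15 = 13 more covariance parameters. The visits are already in the schedule. Including the 3-, 9- and 15-month visits is optional. It raises the count to 55, so it would need a fallback covariance structure, such as heterogeneous Toeplitz, fixed in advance in case the unstructured matrix does not converge.

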#### *Sample size, power calculation & primary outcome*

Because the analysis of the expected primary outcome is concerned with testing superiority of PPD relative to a comunity treatment control group (TAU), we employ an 80% one-sided confidence interval (CI) to assess potential non-inferiority. The trial is powered to detect a 35% difference in effectiveness between PPD and TAU on the Hamilton Depression Rating Scale HRSD-17 [44] with alpha at 0.05 and beta at 0.9. The primary outcome for treatment efficacy is the rating of depressive symptoms by an objective assessor blind to treatment allocation. Estimating effect-size on the basis of previous trials summarized in meta-analyses using the HDRS-17 in psychosocial treatments, with or without pharmacological therapies (e.g. [45]), we could achieve the target levels of alpha and beta with 80 cases randomised equally into two arms. However, this does not take into account within-therapist correlations. Based on statistical analysis of data from another trial of long term psychodynamic therapy with a similarly heterogeneous population [46] we have conservatively assumed an intra-cluster correlation coefficient for therapists of 0.05. With a minimum of 10 therapists delivering each therapy, each seeing on average 5 subjects, the study will have 80% power to reject inferiority with a non-infidelity margin equal to an effect size of 0.5 using an 80% one-sided confidence interval, on the basis of a 90% follow-up rate to 6 months. Given the pragmatic focus of the trial, the degree of adherence to treatment protocols is of considerable interest. The main analyses will be based on an intention-to-treat and complementary “as treated” bases.

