### The treatment as usual condition

Patients randomly assigned to the TAU control group continue to receive treatment as directed by the referring practitioner. This may include referral for other specialist provisions. In the UK’s NHS, the range of such treatments is defined, and to an extent specified, in the treatment guidelines of the National Institute for Clinical Excellence [60]. Referral to psychoanalytic therapy is not within the guidance. Treatments and interventions received by the TAU control participants are recorded over the duration of the trial by using the Client Service Receipt Inventory (CSRI, [61]) and GP records. Arguments for and against this kind of comparison group are considered in the Discussion. At the end of their period of participation in the trial, the cases of all TAU participants are reviewed by the Tavistock’s Adult Department, with a commitment to offer PPD should it be indicated or requested.

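### The as-treated models adjust for receipt of treatment and other post-randomisation variables, so their receipt coefficient contrasts PPD starters with PPD non-starters and is not a treatment effect

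*Protocol article*

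**What the plan says.** Two sections of the protocol article bear on this.

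- **Sample size, power calculation & primary outcome** gives the as-treated analysis its standing: "The main analyses will be based on an intention-to-treat and complementary “as treated” bases". The same section says that adherence is of considerable interest.
- **The analysis of data** sets the order, "An intention-to-treat analysis will be performed in the first instance", and describes a longitudinal model with time as a categorical variable that includes month 0: "The basic model will include the main effects of time, of treatment group", together with the time-by-treatment interaction. It then fixes how the as-treated analysis is done: such "models will be carried out by including variables describing compliance". The examples are "waiting time from randomisation to initiation, degree of participation", and then "including an indicator whether the patient received the study treatment) and auxiliary treatments such as medication".

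No other method for non-adherence is named, and nothing is said about how the resulting coefficients should be read.

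On access to PPD in the control arm, the section on the treatment as usual condition says "Referral to psychoanalytic therapy is not within the guidance". It places the review of TAU patients for PPD after their time in the trial has ended.

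**The concern.** Receipt of therapy and degree of participation are consequences of allocation and of the patient's own state. Waiting time to initiation also arises after randomisation, and it has no natural value for TAU patients or for PPD patients who never start. Medication taken during the trial may respond to treatment.

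If almost nobody in TAU receives PPD, a receipt term can be estimated only by comparing patients inside the PPD arm. The article itself gives a reason to expect that comparison to be selective: its Discussion of randomisation says that some patients drop out through fear of what therapy might involve. A reader who took the receipt coefficient as the effect of having PPD could see benefit where there is none, in an analysis the article lists beside ITT.

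**Working it through.** The plan gives no figure to reproduce. The check concerns what the coefficients mean.

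**Inputs from the article.** The covariates and basic model are as above. The PPD arm has 67 patients (typology sub-study) and the total is 129 (limitations), so TAU has 129 - 67 = 62. Receipt in TAU is taken as zero.

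**Assumed, because the article gives neither.** The share who never start is 20%. Non-starters' outcome is 3 HRSD points worse whatever their allocation. The reference mean is 18. The true effect of receipt is 0 or -4.

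**1. Single-time model, arm and receipt both included, no baseline score.** With receipt = 0 throughout TAU, the arm coefficient is mean(PPD non-starters) - mean(TAU), and the receipt coefficient is mean(PPD starters) - mean(PPD non-starters).

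- TAU mean: 18 + 0.2 × 3 = 18.6. PPD non-starters: 18 + 3 = 21.
- True effect -4: starters 14; arm 21 - 18.6 = +2.4; receipt 14 - 21 = -7.0. PPD mean 0.8 × 14 + 0.2 × 21 = 15.4, so ITT = 15.4 - 18.6 = -3.2 and the complier estimate is -3.2 / 0.8 = -4.0.
- True effect 0: starters 18; arm +2.4; receipt 18 - 21 = -3.0. ITT and complier estimate are both 0.

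**2. Baseline score added (ANCOVA).** If the 3-point gap is already present at baseline and the baseline slope is b, the bias shrinks by the factor (1 - b): receipt -3(1 - b), arm +2.4(1 - b). With b = 0.57, receipt is -3 × 0.43 = -1.3 and arm is 2.4 × 0.43 = +1.0. With a true effect of -4, receipt is -4 - 1.3 = -5.3. If the gap appears only after baseline, adjustment removes nothing and step 1 stands.

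**3. The longitudinal model.** I fitted it by generalised least squares with unstructured covariance to 300,000 simulated patients with complete data, under the same assumptions.

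| Receipt term | True effect | Arm-by-time terms | Receipt coefficient |
|---|---|---|---|
| Constant over time | 0 | about 0 (ITT) | -2.3 to -3.0 |
| Constant over time | -4 | about -3.2 (ITT) | -5.3 to -6.2 |
| Zero at baseline, then 1 if received | 0 | +1.0 to +2.4 | -1.3 to -3.0 |
| Zero at baseline, then 1 if received | -4 | +1.0 to +2.4 | -5.3 to -7.0 |

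Ranges run over whether the prognosis gap is also present at baseline. A time-constant covariate shifts every visit equally and so cancels from the arm-by-time contrast. A time-varying one does not.

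**4. Strength of selection.** A second simulation used a single-time, baseline-adjusted model with 5 to 20% nominal non-start and uptake falling gradually with unmeasured prognosis. At a true effect of 0:

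- moderate selection (log-odds slope 0.5 per SD of prognosis): receipt -0.84 to -0.89;
- stronger selection (slope 1): receipt -1.67 to -1.81;
- no selection: receipt about 0;
- arm term dropped, selective starting: receipt -0.12 to -0.64;
- participation (0 to 1) and medication also added, selective starting: the bias moves to participation, -1.53 to -2.87, and receipt becomes +0.39 to +0.65.

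**5. Medication.** In the same simulation, adding only on-study medication to the arm model moved the arm estimate from -3.59 to -3.12 (true effect -4, 10% non-start unrelated to prognosis).

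**6. Precision where the arm term becomes non-starters versus TAU.** At 20% non-start there are 0.2 × 67 = 13.4 non-starters. Relative to ITT the SE is √(1/13.4 + 1/62) / √(1/67 + 1/62) = 1.7. At 10% it is 2.3 and at 5% it is 3.2.

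**The case against.** The strongest reply is that the article's main model is longitudinal and carries the treatment effect in the arm-by-time interaction. A reader might infer that adding a receipt indicator necessarily turns the arm comparison into non-starters versus TAU. The text does not support that: step 3 shows that a time-constant indicator leaves the interaction at ITT. The article does not say whether receipt is time-varying, whether the as-treated covariates go into the ANCOVA or the longitudinal model, or whether the arm term is kept. This part of the reply stands, and the claim about the arm coefficient must be conditional.

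Three further points stand in part.

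- A reader might infer that every added variable is post-randomisation. Medication is given no timing, and medication at entry is a minimisation factor. On-trial medication is the likelier meaning of auxiliary treatments, but it is not stated. How waiting time is coded in TAU is detail that an article may leave to the analysis plan.
- Absence of PPD in TAU is inferred from the guidance and from the end-of-trial review. It is not documented as a fact.
- The analysis is called complementary and ITT comes first. A reader might infer that the primary result is compromised, but nothing in the article makes it depend on these models.

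The reply does not rescue the receipt coefficient, which is not a treatment effect in any version examined.

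**Conclusion.** The point holds in a limited form. The article commits to a method whose receipt coefficient is a non-randomised contrast, and it names no alternative that respects randomisation. Under the assumed 20% non-start, 3-point gap and no true effect, that coefficient is about -1.3 to -3.0 depending on the model. About -0.9 is plausible with moderate selection, and there is no bias if non-start is unrelated to prognosis. The values +2.4 and -7.0 for a true effect of -4 are the unfavourable end of one set of assumptions and not a prediction for this trial. Distortion of the arm coefficient arises in a single-time ANCOVA that keeps the arm term, or with time-varying receipt, but not with a time-constant indicator in the longitudinal model. The ITT analysis is untouched. This is a moderate matter that should be corrected because the analysis is listed among the main ones and adherence is declared to be of interest.

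**What to change.** Make the estimate of the effect of receiving PPD a complier-average causal effect, with randomised arm as the instrument for receipt, a definition of receipt fixed in advance, and the same baseline covariates as the ITT model.

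- **State the exclusion restriction and its weak point.** Allocation must affect outcome only through receipt. The Discussion of randomisation reports that patients who wanted PPD and were not given it reacted badly, which could breach this. Say so beside the estimate.
- **State the loss of precision.** If uptake is treated as known, the interval is about 1 / 0.8 = 1.25 times as wide as ITT at 20% non-start, and 1 / 0.95 = 1.05 times at 5%. The estimate and its SE are scaled alike, so this adds no power.
- **Prefer a binary definition of receipt.** An estimate per session attended needs a dose-response assumption, which the article's own background section doubts for this therapy.
- **Do not adjust for medication taken after randomisation.** Report it, and other care received, by arm. Baseline medication may stay as a covariate.
- **If a covariate-adjusted as-treated model is kept,** label it exploratory and non-randomised, and say which model it extends and how receipt is coded over time.

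The cost is a little analysis time and a few sentences. Session counts are already recorded for the economic evaluation, and TAU care is already collected from the CSRI and GP records.
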